#### 2. Behavioural assessment and intervention

All participants are asked to fill out a behavioural questionnaire at baseline (V2), in order to collect information about certain habits or behaviours that affect physical, emotional, or mental well-being. During the 10-week intervention period, both groups are enrolled in a behavioural programme delivered through ONMI’s App with 2–3 electronic push notifications per week. Subjects randomised to the personalised group receive behavioural prompts (active Do’s) from the predefined ONMI’s evidence-based behavioural change programme, which has been developed to increase behavioural flexibility and facilitate adoption of healthier habits.^40^ For the purposes of this trial, the personalised group Do’s (from ONMI) are based on subject’s reports from the behavioural questionnaire at V2 in addition to inputs from the nutritional recommendations (from the Eurecat Nutrition Team) via the PREVENTOMICS platform, to provide a comprehensive behavioural change and improve adherence to the dietary intervention. For example, if a participant was recommended to eat kale and brussels sprouts, they could get a message like: *‘*Our analysis shows kale and brussels sprouts are good for you and should be part of your diet. Find out how much you should be consuming. Do it now’. Table 4 illustrates the different types and quantity of the Do’s and massages delivered to personalised and control groups. The messages delivered to the control group are not personalised and are mostly informational in nature rather than prompting participants to take a specific action (ie, general guidelines available from the National Health Service and the WHO). The personalised and control groups receive the same behavioural treatment in terms of volume (frequency and intensity); the content of messages differs between groups as reflected in the numbers of specific types of messages delivered to each group, but the total number of messages is very similar (table 4).

**Table 4 T4:** The type and number of behavioural messages delivered by ONMI to the participants in the personalised and control groups

Type of messages	Quantity	Description	Example	PP	C
Starter Do	1	Easy start of the programme on behavioural questionnaire completion at V2	SWITCH SEATS DAY! Move some seating around today. Sit somewhere different at meals/ when working/when watching TV. Get a new view!—Shaking up old habits is good for you and puts you back in charge of your life. Try something new regularly. Make every day count! --	✓	✓
General Do	5	Apply to everyone, relatively easy, to get user hooked to the programme	NEW WAY DAY. Take a detour today, go the prettiest route not the shortest. Allow more time, smile at people. Spot 3 beautiful things along the way.—Wakey Wakey. Regularly challenging our brain keep us alert and interesting. When we take notice of our surroundings we start to live life to the fullest.	✓	
Personalised Do	10	Based on behavioural questionnaire	WHAT ARE YOU EATING FOR? Back off from boredom, address your stress. Get busy, unwind, release your emotions so you only eat when you're hungry today.	✓	
System Message	3	Encouragements, tips, manage expectations	HEALTH TIP. Regular contact with friends and family is key to good mental and physical health. Connections give meaning and purpose to our lives, even when it is digitally.	✓	
Expander Do	3	Prompt user to explore new parts of personality, based on behavioural questionnaire	EXPANDER: It’s NO Day today. Don't say yes when you really want to say no. Give no reason or excuse. Just say, 'Sorry, but the answer’s no'.	✓	
Preventomics Messages	6	Template messages that use inputs from the nutritional recommendations of food to increase	PREVENTOMICS: Are you getting the right amount of {{.R1}} and {{.R2}} in your diet? Go online and find some interesting recipes to try at home. Do it now.	✓	
General Messages	24	Recommendations from the NHS and WHO on eating, eating out, exercise, check-ups, help and support, balanced diet	Eating a healthy, balanced diet is an important part of maintaining good health, and can help you feel your best. This means eating a wide variety of foods in the right proportions, and consuming the right amount of food and drink to achieve and maintain a healthy body weight.		✓

C, control; NHS, The National Health Service; PP, personalised plan; PREVENTOMICS, Empowering consumers to PREVENT diet-related diseases through OMICS sciences; WHO, World Health Organization.

### Compliance and food intake biomarkers

Dietary adherence is assessed twice a week—through an electronic questionnaire—by reporting the proportion of food consumed from the meals provided by Simple Feast in the previous 3 days. For example, in response to the question *‘*How much of your breakfast did you eat on day 1*?*’ the possible answers can be: (1) Nothing or very little (0%–30%); (2) Approximately half (30%–70%); (3) Almost everything or everything (70%–100%).

Overall compliance to the diet and the behavioural programme is measured at the end of the trial by a six-point Likert scale question ranging from 1 (not at all compliant) to 6 (completely compliant). In addition, objective measures of adherence to the nutrition intervention will be evaluated: urine collected at prebaseline and the end-of-trial visits will be analysed for the quantification of selected biomarkers of food intake through a target ultra-performance liquid chromatography-ion mobility separation-high resolution mass spectrometry approach at the University of Parma (UNIPR, Italy). In particular, a set of about 150 potential biomarkers of intake related to major food groups (tubers, cereals, legumes, vegetables, fruits, nuts, vegetable oils, dairy products, meat, fish and alcoholic beverages; among others) and, when available, specific foodstuffs (orange, apple, cocoa, etc) will be defined on the basis of available literature and the technical feasibility at the time of the sample analysis. Data on biomarkers of food intake will also serve to assess the validity of the information collected through 3-day food diaries at prebaseline and end-of-trial visits.

### Data collection and outcome measures

Data are collected at screening, prebaseline (V1), baseline (V2) and 10 weeks after initiating the intervention (V3) by using self-reported questionnaires, biological specimens, accelerometers and physical examinations conducted by trained local research staff in accordance with standard operating procedures (table 5). All primary and secondary endpoints are derived from measurements obtained at baseline (V2) and at the end of the intervention (V3). Measurements taken prebaseline (V1) were used for clustering assignment. Reminder text messages are being sent to the participants before visit days. It is expected that a high retention rate will be achieved due to the nature of the study.

**Table 5 T5:** Procedures and activities during the study period

	Screening visit (V0)	Pre-baseline visit (V1)	Baseline visit (V2)	End of trial visit (V3)
**Week**	−**20 to −13**	−**9 to −6**	**0**	**10**
**Visit day**	**0**	**1**	**2**	**3**
Informed consent	X			
Review of inclusion and exclusion criteria	X			
Medical history and examination	X			
Randomisation			X*	
Registration of medication and adverse events	X	X	X	X

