**Anthropometry**				
Body weight	X	X	X	X
Height	X			
Waist circumference	X	X	X	X
Body composition (DXA)			X	X

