### Secondary outcomes

#### Anthropometry and body composition

Subjects' body composition is measured using a whole body DXA scan. Body weight is measured at all visits using a calibrated digital scale to the nearest 0.1 kg with participants wearing lightweight clothes and no shoes, as well as after voiding their bladder. Height is measured at the screening visit using a wall-mounted stadiometer to the nearest 0.5 cm while participants are not wearing shoes. BMI (kg/m^2^) is calculated as weight in kilograms divided by height in metres squared. Waist circumference (cm) is measured with a stretch‐resistant tape at the midpoint between the lower margin of the last palpable ribs and the top of the iliac crest, in the fasted state (non-fasted during the screening visit) with an empty bladder and with participants wearing light clothes. Each measurement is taken twice to the nearest 0.5 cm and the average is used.

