#### Biological samples

Fasting blood samples collected at prebaseline, baseline and week 10 are analysed for plasma glucose, insulin, adipokines (leptin and adiponectin), inflammatory biomarkers (CRP, IL-6, IL-10, TNF-α, MCP-1, sICAM-1, sCD-14), lipid profile (total cholesterol, LDL-cholesterol, HDL-cholesterol, oxLDL, triglycerides), liver biomarkers (ALT and GGT) and renal biomarkers (uric acid, creatinine). Blood samples are sent to Eurecat for metabolomics analysis while biochemical markers are measured at NEXS, University of Copenhagen.

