#### Blood pressure

Systolic and diastolic blood pressures and heart rate are measured by an automatic sphygmomanometer on the arm after 5–10 min rest in a sitting position. The same arm is used during all visits. The measurement is repeated three times (or four, if the last two measurements deviate by >5 mm Hg), approximately 1 min apart, and readings are recorded to the nearest 1 mm Hg for blood pressures and 1 bpm for heart rate. The average of the last two readings is used.

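### Blood pressure and the fasting blood markers have a second pre-treatment value (V1) that is given only a clustering use; adding it as a covariate would bring a modest gain in precision

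*Protocol article*

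**What the plan says.** Under Data collection and outcome measures, the protocol article fixes the visits behind the endpoints: "All primary and secondary endpoints are derived from measurements obtained at baseline (V2) and at the end of the intervention (V3"). The next sentence gives the role of the earlier visit: "Measurements taken prebaseline (V1) were used for clustering assignment".

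Several secondary outcomes are nevertheless measured at both visits.

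- **Blood markers.** Under Biological samples: "Fasting blood samples collected at prebaseline, baseline and week 10 are analysed for plasma glucose, insulin", followed by the adipokines, inflammatory markers, lipids, and liver and renal markers.
- **Blood pressure.** Table 5 marks it at V1, V2 and V3. Within a visit it is measured at least three times, and "The average of the last two readings is used".
- **Weight and waist.** Table 5 marks both at V1, V2 and V3, and also at screening. For weight: "Body weight is measured at all visits using a calibrated digital scale to the nearest 0.1 kg".
- **DXA body composition.** Table 5 marks it at V2 and V3 only.

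Table 5 places V1 at weeks −9 to −6, V2 at week 0 and V3 at week 10, and notes that randomisation takes place before the V2 visit. Recruitment procedure reports that one hundred participants completed V1. Statistical analysis describes a linear mixed model with time, group and their interaction for the primary objective. Its covariates (sex, age, baseline BMI) are given as examples, to be used as necessary. No model is stated for the secondary outcomes.

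**The concern.** The trial was sized on fat mass alone, so the precision of the long list of secondary markers is whatever 82 completers happen to give. Many of these markers vary a good deal within a person from one visit to the next, and for such a marker a single V2 value is an imperfect measure of the person's usual level. A second pre-treatment value carries information about that level, and here it has been measured in everyone who reached clustering.

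If the model given for the primary objective were carried over to the secondary outcomes, then with complete data at two visits its time-by-group term would equal the between-group contrast in V3 − V2. V1 would contribute nothing. At stake is the width of the confidence intervals for the noisy secondary markers. The primary result and the validity of any comparison are not at stake.

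**Working it through.** **The plan's own figure.** For a difference of 1.25 kg, SD 2.0 kg, 80% power and two-sided 5%, n per group = 2 × (1.96 + 0.84)² × (2.0/1.25)² = 40.1, or 41 after rounding up; the exact t-test calculation gives 41.2. Allowing for 18% dropout, 41/0.82 = 50 per group. The stated 41 and 50 reproduce. The point leaves them unchanged, because fat mass has no V1 value.

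**Formulas.** Take the single-visit variance as 1, with a = corr(V1,V2), b = corr(V2,V3) and c = corr(V1,V3). The variance of the group contrast is proportional to:

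- change score V3 − V2: 2 − 2b
- V3 adjusted for V2: 1 − b²
- V3 adjusted for V1 and V2: 1 − (b² + c² − 2abc)/(1 − a²)

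The article gives none of these correlations, so every value below is an assumption.

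**Case 1: equal correlation ρ between all visits.** The last formula becomes 1 − 2ρ²/(1 + ρ).

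| ρ | Change score | V2 only | V1 and V2 | Cut due to V1 | Cut versus change score |
|---|---|---|---|---|---|
| 0.5 | 1.00 | 0.75 | 0.667 | 11% | 33% |
| 0.8 | 0.40 | 0.36 | 0.289 | 20% | 28% |

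**Case 2: correlation decaying with time, plus visit noise.** This fits the schedule better, since V1 lies 16-19 weeks before V3 and V2 lies 10. Let R be the reliability of one visit and r the true-score correlation over 10 weeks, with V1 taken 7.5 weeks before V2. Then a = R·r^0.75, b = R·r and c = R·r^1.75.

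| R | r | Change score | V2 only | V1 and V2 | Cut due to V1 | Cut versus change score |
|---|---|---|---|---|---|---|
| 0.50 | 0.80 | 1.200 | 0.840 | 0.805 | 4% | 33% |
| 0.70 | 0.95 | 0.670 | 0.558 | 0.490 | 12% | 27% |
| 0.85 | 0.80 | 0.640 | 0.538 | 0.522 | 3% | 18% |
| 0.85 | 0.95 | 0.385 | 0.348 | 0.307 | 12% | 20% |

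Over R from 0.5 to 0.85 and r from 0.8 to 0.95, V1's own cut is 3-12%, and the cut against the change score is 18-33%.

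**Case 3: a stable measure such as weight.** With R = 0.98, V1 cuts variance by 0-2%. Averaging V1 into the baseline of a change score would raise its variance by 5-8%.

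**How much of the larger cut is due to V1.** In Case 1 at ρ = 0.5, going from 1.00 to 0.75 is conditioning on V2 and accounts for 25 of the 33 points. At ρ = 0.8, going from 0.40 to 0.36 accounts for 10 of the 28. In Case 2, conditioning on V2 supplies about half (R = 0.85, r = 0.95) to nine tenths (R = 0.50, r = 0.80: 30 of 33 points).

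**Bias.** A simulation took 100 participants with five cluster scores and correlation 0.7 between visits. Cluster was the highest V1 score, allocation was in blocks of two within cluster, and there were 6,000 runs without a treatment effect. The mean group contrast was −0.002 with V1 in the model, so selecting clusters on V1 does not bias the randomised comparison. The variance ratio for V1 and V2 against V2 alone was 0.85. Within a cluster the defining score fell by 0.35 SD from V1 to V2. That is regression to the mean, and a reason not to use V1 as the baseline for describing change.

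**The case against.** The strongest reply is that nothing here is stated wrongly. The sentence on V2 and V3 defines the endpoints and does not list or bar covariates, so it could stand word for word with V1 added to a model. The last visit before treatment is the usual baseline, and here it also avoids the values on which clusters were selected. All of this stands, and it is why the point is one of efficiency only.

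A reader might infer that the plan throws the V1 data away. The article does not show that. Its one model is for the primary objective, its covariates are left open, and an analysis plan that is not shown may already use V1.

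A reader might also take the cut of 28-33% against a change score, equivalent to 39-50% more participants, as the value of V1. It is not: part of it, and at low correlation most of it, comes from conditioning on V2. Relative to adjusting for V2 alone, the equal-correlation figures correspond to a factor of 1.12-1.25 in effective sample size (0.75/0.667 and 0.36/0.289), and Case 2 gives less.

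Two further objections stand. Weight does not belong among the outcomes that gain. And cluster adjustment is not in the calculation: since clusters are built from V1 biomarkers, V1 may add somewhat less once cluster is in the model. None of this makes the proposed adjustment unsound.

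**Conclusion.** The point holds as an optional improvement for noisy secondary outcomes measured at both V1 and V2. Adding V1 to a model that already contains V2 would cut variance by about 3-12% under decaying correlation with visit noise, and by 11-20% under equal correlation of 0.5-0.8, which is the favourable case. Both ranges rest on assumed correlations and leave out cluster. The gain is near zero for stable measures such as weight. DXA outcomes, primary or secondary, cannot benefit. The choice of V2 as baseline and the sample size are sound, and the documents do not contradict themselves here.

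**What to change.** Keep V2 as the baseline for describing change. Add one sentence to the statistical analysis section or the analysis plan: for noisy secondary outcomes measured at both visits (for example CRP, IL-6, insulin, HOMA-IR, triglycerides and blood pressure), the V3 value is modelled on group, V2 value, V1 value and metabolic cluster, the randomisation stratum. Do not average V1 into the baseline. Name the outcomes and settle the model before the code is broken, because the current covariate wording is open and a later addition would look driven by the data.

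The cost is one degree of freedom for V1 and four for the five clusters. With 82 completers, residual degrees of freedom fall from 82 − 3 = 79 (intercept, group, V2) to 82 − 8 = 74. No new measurement is needed.

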**Anthropometry**				
Body weight	X	X	X	X
Height	X			
Waist circumference	X	X	X	X
Body composition (DXA)			X	X
**Biological samples**				
Fasting blood sample		X	X	X
Saliva sample (SNPs)		X		
Urine sample		X	X	X
Faecal sample			X^†^	X^†^
**Nutritional assessment**				
Food Frequency Questionnaire		X		X
3-day dietary records		X^†^		X^†^
**Other measurements**				
Blood pressure/heart rate		X	X	X
Three factor eating questionnaire			X	X
Perceived Stress Scale			X	X
Behavioural questionnaire (by ONMI)			X	X
Quality of Life questionnaires			X	X
Diet satisfaction questionnaire (DSat-28)			X	X
Money spent on food questions			X	X
Accelerometer (sleep and PA)		X^‡^	X^‡^	

*Prior to visit.

†At home activity prior to visit.

‡At home activity following the visit.

DXA, dual-energy X-ray absorptiometry; PA, physical activity.

### Primary outcome

The primary endpoint is the difference in body fat mass (kg) from baseline to end of trial between the two intervention groups (personalised vs control). Body fat mass is determined during body composition analysis by use of dual-energy X-ray absorptiometry (GE Healthcare Lunar, Madison, Wisconsin, USA). The participants are scanned in a fasted state, lying on their back wearing lightweight clothes without jewellery and other metallic objects.

### Secondary outcomes

#### Anthropometry and body composition

Subjects' body composition is measured using a whole body DXA scan. Body weight is measured at all visits using a calibrated digital scale to the nearest 0.1 kg with participants wearing lightweight clothes and no shoes, as well as after voiding their bladder. Height is measured at the screening visit using a wall-mounted stadiometer to the nearest 0.5 cm while participants are not wearing shoes. BMI (kg/m^2^) is calculated as weight in kilograms divided by height in metres squared. Waist circumference (cm) is measured with a stretch‐resistant tape at the midpoint between the lower margin of the last palpable ribs and the top of the iliac crest, in the fasted state (non-fasted during the screening visit) with an empty bladder and with participants wearing light clothes. Each measurement is taken twice to the nearest 0.5 cm and the average is used.

#### Biological samples

Fasting blood samples collected at prebaseline, baseline and week 10 are analysed for plasma glucose, insulin, adipokines (leptin and adiponectin), inflammatory biomarkers (CRP, IL-6, IL-10, TNF-α, MCP-1, sICAM-1, sCD-14), lipid profile (total cholesterol, LDL-cholesterol, HDL-cholesterol, oxLDL, triglycerides), liver biomarkers (ALT and GGT) and renal biomarkers (uric acid, creatinine). Blood samples are sent to Eurecat for metabolomics analysis while biochemical markers are measured at NEXS, University of Copenhagen.

#### Blood pressure

Systolic and diastolic blood pressures and heart rate are measured by an automatic sphygmomanometer on the arm after 5–10 min rest in a sitting position. The same arm is used during all visits. The measurement is repeated three times (or four, if the last two measurements deviate by >5 mm Hg), approximately 1 min apart, and readings are recorded to the nearest 1 mm Hg for blood pressures and 1 bpm for heart rate. The average of the last two readings is used.

### Other outcome measures

#### Saliva

Saliva samples were collected prebaseline and sent to Alimentomica (University of the Balearic Islands, Palma de Mallorca) for analysis of genetic variants, mainly SNPs in genes related to metabolism, inflammation, and oxidative stress for cluster assignment. Currently, there are 188 candidate SNPs being analysed and validated in an ongoing trial and a minimum of 35 and maximum of 150 SNPs of those are expected to be used in this study.

#### Urine samples

Participants were asked to deliver a second-void urine spot sample in the morning at pre-baseline, and do the same at baseline and end of the study visits. Urine samples from prebaseline and week 10 are used by UNIPR for food intake biomarker analysis and by Eurecat for analysing markers of oxidative stress used in cluster assignment. Furthermore, aliquots of urine samples from all visits are stored in a biobank for future analyses.

#### Nutritional assessment

Dietary intake is assessed pre-baseline and at the end of the study by using a validated self-administered electronic form of the European Prospective Investigation of Cancer-Norfolk Study food frequency questionnaire,^41^ supervised by a trained staff member. Furthermore, participants are instructed to complete 3-day weighed food records during the week before the pre-baseline visit and during the third week of the intervention. The dietary records cover two non-consecutive weekdays and 1 weekend day. Nutrient analysis will be done by the software program Vitakost (Conava ApS; Kolding, Denmark), which is based on the Danish national food database.

#### Questionnaires

**Eating behaviour** assessment at baseline and week 10 is conducted by administrating the three factor-eating questionnaire.^42^ This is a 51-item self-report questionnaire which measures three domains of eating behaviour: (1) cognitive restraint of eating, (2) disinhibition and (3) hunger.

**Stress** assessment is conducted through the 10-item perceived stress scale (PSS)^43^ at baseline and week 10. The PSS is one of the most widely used psychological instruments. It measures the degree to which participants perceive events in their life as being stressful by asking about thoughts and feelings over the last month using a response scale from 0 (never) to 4 (very often).

**Quality of life** is assessed by two questionnaires at baseline and week 10: (1) The EuroQol five-diminsion five-level (EQ-5D-5L),^44^ which is a standardised instrument developed by EuroQol Group for measuring health-related quality of life on five dimensions (mobility, self-care, usual activities, pain/discomfort and anxiety/depression), with five response levels per dimension, and also includes a Visual Analogue Scale (EQ) by which respondents report their perceived health status and (2) Obesity and Weight-Loss Quality of Life Instrument,^45^ which is an instrument consisting of 17 statements about weight-related feelings and emotions which are rated on a seven-point scale, and primarily measures emotions and feelings resulting from suffering from obesity and trying to lose weight.

**Diet satisfaction** is assessed at baseline and week 10 by the Diet Satisfaction Questionnaire (DSat-28)^46^ that involves 28 statements grouped into five dimensions (healthy lifestyle, eating out, cost, preoccupation with food and planning and preparation) to evaluate satisfaction with weight-management diets.

**Food expenditure** is assessed by two questions completed at baseline and week 10 regarding the amount of money spent on food for the whole household.

